## Abstract

**Background:**

Vaginal discharge (VD) is a common health concern among women of reproductive age worldwide. In low- and lower-middle-income countries (LLMICs), one in four women experiences distressing VD which may indicate underlying infections. About one-third of these cases are caused by one of three curable sexually transmitted infections (STIs)*—Chlamydia trachomatis [Ct]*, *Neisseria gonorrhea [Ng], Trichomonas vaginalis [Tv]*—or by bacterial vaginosis (BV). Syndromic management, the standard approach to care in LLMICs, relies on empirical antibiotic treatment, often resulting in overtreatment and contributing to antimicrobial resistance. To reduce unnecessary use of antibiotics, affordable, accurate, and rapid diagnostic tests such as point-of-care tests (POCTs) are needed—particularly in settings where over-the-counter antibiotic use is common and psychosocial problems may be somatized. Additionally, education on VD and appropriate antibiotic use, along with recognition of mental health or domestic violence issues, may be important for facilitating acceptance of POCTs.

**Methods:**

This study is a randomized controlled double-blind, superiority trial with follow-up assessments at 4 weeks and 4 months conducted in a Nepalese teaching hospital and its outreach centers. Participants are randomly assigned to one of three study arms: Arm 1 receives treatment, based on syndromic management; Arm 2 receives POCT-guided treatment using the *Cepheid GeneXpert®* (for *Ct* and *Ng*), pH and whiff tests (for BV and *Tv*), and the *OSOM®* test (for *Tv*); Arm 3 receives the same POCT-guided treatment as Arm 2, plus an educational intervention, and referral for psychosocial concerns. The primary outcome is the proportion of participants overtreated with antibiotics at the primary consultation, comparing Arm 1 versus Arms 2 and 3. Secondary outcomes include over-the-counter antibiotic acquisition, subsequent health-seeking behavior, and changes in VD symptom development over time.

**Discussion:**

The trial assesses the effectiveness and impact of integrating POCTs into VD management in a resource-limited setting. Results of comparing syndromic-based management with POCT-guided diagnostic testing and treatment, both alone and combined with psychosocial and education-based interventions, inform strategies to reduce antibiotic overuse and improve broader reproductive health concerns.

**Trial registration:**

ClinicalTrials.gov NCT05977491. Registered on 8 April 2023. https://clinicaltrials.gov/study/NCT05977491?cond=vaginal%20discharge&rank=6

**Protocol version:**

Version 6, October 30, 2025.

**Supplementary Information:**

The online version contains supplementary material available at 10.1186/s13063-025-09333-4.

## Background

Women of reproductive age are frequently bothered by vaginal discharge (VD), leading many to seek care at gynecological outpatient departments (OPDs) [1]. VD can be physiological or pathological. Hormonal fluctuations influence physiological VD, while sexually transmitted infections (STIs), candidiasis, and bacterial vaginosis (BV) are the most common pathological causes of abnormal VD. All these conditions typically involve changes in the color, consistency, amount, or odor of the discharge [2].

Approximately one-quarter of adult women in South Asia report bothersome VD for which they seek medical care [3, 4]. A population-based study in Nepal found that while 34% of women self-reported bothersome VD, only 25.7% exhibited abnormal physical findings on gynecological examination [5]. In a tertiary hospital OPD setting in Nepal, an unpublished study found self-reported VD concerns in 28% of women, comparable to the 24.6% prevalence reported in a similar setting in India [6, 7].

Among women presenting with bothersome VD in clinical settings, approximately one-third are found to have one or more of three treatable STIs—*Chlamydia Trachomatis* (*Ct*), *Neisseria gonorrhea* (*Ng*), *Trichomonas vaginalis (Tv)*—or to have BV, which is caused by an imbalance of the vaginal flora and is not currently classified as an STI [8–10]. STIs and their aftereffects are common in low- and lower-middle-income countries (LLMICs), particularly in Southeast Asia. In a population-based study conducted in Nepal, curable STI pathogens were detected in 6.8 to 9.4% of women who either reported abnormal VD or had it confirmed by gynecological examination [5, 11–13].

In 1984, the World Health Organization (WHO) endorsed syndromic management guidelines for STIs in LLMICs, where etiologic STI diagnosis is often unavailable. This comprehensive and cost-effective approach relies on observed signs, symptoms, and risk factors to guide empirical treatment for *Ct*, *Ng*, *Tv,* BV, and candidiasis at the initial point of contact with the health care system [14, 15]. To date, syndromic management remains the standard of care for STIs in Nepal [15]. However, this approach has particularly low diagnostic accuracy for cervical infections caused by *Ct* and *Ng*, often leading to overtreatment with broad-spectrum antibiotics such as cephalosporins, azithromycin, and doxycycline. This has raised concerns about antimicrobial resistance (AMR), especially in *Ng*, where treatment options are limited [14]. AMR has been identified by the WHO as one of the top global health threats [16], and *Ng* is now designated a high-priority AMR pathogen in the 2024 WHO bacterial priority list [17]. These limitations underscore the need for accurate diagnostic tools and more targeted antibiotic use.

To address these challenges, the WHO’s 2021 *Global Health Sector Strategy* recommends etiological STI treatment wherever feasible, as part of the goal to end the STI epidemic by 2030 [18, 19]. While molecular tests are considered the gold standard for STI diagnosis, their use has been largely limited to high-income countries due to high cost, infrastructure requirements (such as the need for laboratory facilities), need for trained personnel, and lengthier turnaround time for results [18, 20]. The WHO has therefore advocated for point-of-care tests (POCTs) that preferably fulfill the ASSURED criteria—affordable, sensitive, specific, user-friendly, rapid and robust, equipment-free, and deliverable to end users [21]. POCTs offer fast results and allow more precise antibiotic treatment, potentially benefiting both patients and sexual partners. Highly accurate POCTs based on nucleic acid amplification tests (NAATs) offer 90–100% sensitivities and specificities, though they remain quite expensive [22]. The Cepheid *Ct/Ng* molecular POCT, for example, has demonstrated over 95% sensitivity and specificity, with a 90-minute turnaround time [22]. However, cost remains a barrier, particularly in LLMICs. To address affordability while maintaining diagnostic accuracy, alternative types or combinations of POCTs may be needed [14]. Extremely low-cost, non-molecular POCTs such as pH testing and confirmatory whiff tests have shown sensitivity and specificity above 87% for BV. However, sensitivity for *Tv* remains low (51.8%), though specificity is higher (78.8%) [23, 24]. Antibody-based POCTs such as the *OSOM®* test offer better sensitivity and specificity and remain relatively affordable for *Tv* detection [25].

Despite these advantages, POCTs have not been widely implemented. Barriers include affordability, lack of quality assurance systems, insufficient clinician support, site-specific logistical issues, and limited awareness among clinicians and patients [26–28]. Over-the-counter (OTC) antibiotic access also complicates efforts to control AMR; in many settings, more than half of antibiotics are purchased from a pharmacy without a medical prescription, contributing to the growing burden of AMR [29, 30]. Even if POCTs reduce unnecessary prescriptions of antibiotics, it is unclear whether women will adhere to restrictive treatment advice in South Asia, where reproductive health literacy is often low [31]. No studies to date have examined whether education on VD and antibiotic use might enhance treatment adherence or POCT acceptability. Moreover, a large proportion of women reporting bothersome VD do not have STIs [5]. In such cases, symptoms may reflect underlying common mental health conditions or trauma from experiences of sexual or domestic violence (DV) [3, 32–34]. Addressing these factors could improve VD management overall and help reduce unnecessary antibiotic use.

## Methods/design

### Aim

This study evaluates whether implementing a combination of highly accurate and simple POCTs for the management of bothersome VD in healthcare settings in Nepal can reduce antibiotic overtreatment compared to the syndromic management approach. It also examines the impact of incorporating education and attention to psychosocial concerns on outcomes such as OTC purchase of antibiotics, symptom development, and patient satisfaction. In addition, the study assesses the diagnostic accuracy of a combination of POCTs for *Tv* and BV—both combined and individually.

### Trial design

This study is a randomized, controlled, double-blinded superiority trial. Study participants are randomly allocated into three parallel arms in a 1:1:1 ratio. The trial arms are as follows: 1. Treatment as usual, 2. Treatment based on POCT results, and 3. Treatment based on POCT results combined with education about VD and antibiotics and addressing psychosocial vulnerabilities (see Fig. 1).

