### Outcomes

The primary outcome measures are:The proportion of participants overtreated with antibiotics at the primary consultation with the health practitioner Overtreatment is defined as receiving a cephalosporin and/or macrolide when *Ng* is negative; a tetracycline or macrolide when *Ct* is negative; or a nitroimidazole when the gold standard test for *Tv* or BV is negative, (medications as specified in the Nepali STI case management guidelines) [15] (comparing arm 1 with the combined arms 2 and 3).The proportion of participants prescribed AMR driving antibiotics (Cephalosporins, Azithromycin, Ciprofloxacin) at the primary consultation with the health practitioner. comparing treatment as usual (arm 1) with POCT-based treatment (arms 2 and 3).The proportion of participants adhering to treatment recommendations, comparing arms 2 and 3. Adherence is assessed during telephone follow-ups after one month and is defined as follows: (a) participants report that they took the prescribed medication; (b) no additional purchase of antibiotics; and (c) no purchase of other medication for VD.

The study also examines six secondary outcome measures at various time points. The baseline data from this trial will also contribute to the analysis of the epidemiology of VD and infection including psychosocial factors, and measure the diagnostic accuracy of the POCT.

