### Randomization and blinding

After obtaining informed consent, RAs open consecutively numbered, sealed opaque envelopes containing the randomized group assignment. Randomization is computer-generated using a simple randomization method (Research Randomizer©). Participants are blinded to their group assignment. Each PID (1–1500) was assigned to one of the three trial arms (1, 2, 3) based on pseudo-random numbers uniformly distributed between 0 and 1, with equal probability of allocation to each group.

The resulting allocation list was generated by an independent researcher and implemented on site using consecutively numbered, sealed opaque envelopes containing the randomized group assignment. We opted not to stratify or block to keep field procedures straight forward and robust in this multi-site and resource-limited setting. This reduced the risk of errors in envelope handling and simplified implementation for rotating staffs. Due to the nature of the intervention, only RAs performing follow-up and the statistician are blinded to group allocation. HPs are informed about whether they will receive POCT results but blinded as to whether participants receive educational materials or are offered counseling (arm 1 vs. arm 2 and 3).

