#### Laboratory diagnostics

Gold standard STI testing includes the following: *Cepheid GeneXpert*® for *Ct*, *Ng,* and *Tv*. For BV, dried wet mounts from vaginal smears are collected for Nugent scoring and wet mount microscopy. All tests are performed by RAs, except Nugent scoring (performed by microbiologist [name]) and wet mount microscopy (performed by [name]). Nugent scoring is considered the gold standard for BV. For quality control, 10% of slides are double read by a second microbiologist ([name]).

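### The trial is labelled double-blind, but prescribers know the Arm 1 versus Arms 2+3 split that defines two of the three primary endpoints, and the blinding section contradicts itself

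*Protocol article*

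**What the plan says.** The abstract's Methods paragraph opens: "This study is a randomized controlled double-blind, superiority trial with follow-up assessments at 4 weeks and 4 months". Trial design repeats it: "This study is a randomized, controlled, double-blinded superiority trial". Neither place qualifies the term.

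Randomization and blinding then makes three statements about who is blinded:

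- On participants: "Participants are blinded to their group assignment".
- On everyone else, after noting that the nature of the intervention limits blinding: "only RAs performing follow-up and the statistician are blinded to group allocation".
- On prescribers: "HPs are informed about whether they will receive POCT results", although they are "blinded as to whether participants receive educational materials or are offered counseling". A parenthesis naming arm 1 against arms 2 and 3 follows directly.

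Outcomes defines primary endpoint (a) as "The proportion of participants overtreated with antibiotics at the primary consultation with the health practitioner". Endpoint (b) is the proportion prescribed AMR-driving antibiotics at that same consultation. Primary outcome analyses compares both between Arm 1 and Arms 2+3 combined. Endpoint (c), adherence at the one-month telephone call, compares Arm 2 with Arm 3. Under Prescriptions and antibiotic use, the practitioner fills in the form that documents what was prescribed.

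**The concern.** An unqualified double-blind label tells the reader that knowledge of allocation cannot have shaped the outcome. Here the person whose decision is the outcome, and who writes it down, knows which side of the comparison the patient is on. The two blinded groups named in the restrictive sentence do not protect endpoints (a) and (b). Those endpoints are complete at the first consultation, before follow-up starts, and a blinded statistician cannot undo what happened in the consulting room.

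The stake is what may be claimed about bias for the headline comparison. Anyone grading risk of bias from the abstract or the design statement would credit a protection that this comparison lacks. Someone who goes on to the blinding section cannot tell from it whether participants are blinded, or which arm split is hidden from prescribers.

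**Working it through.** The point involves no figure, so the check sets the passages side by side.

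**Step 1: what the prescriber knows.** Under Trial arms, POCT results are withheld from the practitioner in Arm 1 and supplied in Arms 2 and 3. Knowing whether results will come is therefore the same as knowing Arm 1 versus Arms 2+3. It does not reveal Arm 2 versus Arm 3, because the practitioner is not told about the educational material or the counselling.

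**Step 2: match that knowledge to each primary endpoint.**

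| Primary endpoint | Contrast | Whose act | Who records it | Contrast known to that person? |
|---|---|---|---|---|
| (a) Overtreatment | Arm 1 vs 2+3 | Practitioner | Practitioner | Yes |
| (b) AMR-driving antibiotics | Arm 1 vs 2+3 | Practitioner | Practitioner | Yes |
| (c) Adherence at one month | Arm 2 vs 3 | Participant | Follow-up research assistant | No, if both are blinded as stated |

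The label fails for (a) and (b), two of the three. It has support for (c), where the prescriber is also blinded to the contrast.

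**Step 3: consistency of the sentences on participants.** One sentence says participants are blinded. A later one in the same section says that only follow-up research assistants and the statistician are. If the second list is complete, the first sentence is false. If the first is true, the list is not complete. Both cannot stand.

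**Step 4: the parenthesis.** It follows what practitioners are blinded to, but it names arm 1 against arms 2 and 3. By Step 1 that is the split they know. The split concealed from them is Arm 2 versus Arm 3. Read literally, the sentence says practitioners are blinded to the comparison that its own first half says they can see.

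**Step 5: is the limitation acknowledged elsewhere?** The limitations paragraph of the Discussion covers the cost of the Ct/Ng test and the omission of fungal infection. Prescriber unblinding is not among them.

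**The case against.** The strongest reply is that nothing is hidden. The intervention consists of giving the prescriber a test result, so prescribers cannot be blinded to it. The blinding section says so and nowhere claims that they are blinded to receiving results. The article also describes real masking: participants are stated to be blinded, Arms 1 and 2 both watch a general health video, follow-up callers and the statistician are blinded, and prescribers do not know Arm 2 from Arm 3. Much of a statement by role is already there.

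Most of this stands, and it limits the point to the label and the wording. It does not rescue the label, because disclosure in a later section does not correct an unqualified claim in the abstract and the design statement. Nor does it resolve the two contradictions within the blinding section.

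Two stronger readings are tempting, and the documents do not support them:

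- A reader might infer that prescribers know the full allocation. They know only Arm 1 versus Arms 2+3.
- A reader might infer from the restrictive sentence that the microbiologists scoring slides for bacterial vaginosis are unblinded. This would matter, because "Nugent scoring is considered the gold standard for BV" and the score helps decide whether a nitroimidazole counts as overtreatment. But the same sentence would also exclude participants, who are expressly said to be blinded, so it is not a reliable complete list. The article does not say whether slide readers are masked, and a condensed article may leave that to the full protocol. Silence is not evidence that they know the arm.

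It is also conjecture that Arm 1 prescribing shifted because practitioners knew they were treating a comparator patient. Randomization is by participant and practitioners are trained on POCT accuracy, so the route is conceivable, but nothing in the article shows that it happened or in which direction.

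**Conclusion.** The point holds as an error of labelling and internal consistency. The double-blind claim is wrong for primary endpoints (a) and (b), because the people who make and record those outcomes know the contrast being tested. The blinding section contradicts itself on participants, and its parenthesis names the wrong arm split.

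The size is two of three primary endpoints, including the headline comparison. No bias in percentage points can be derived from the documents, and none is claimed. No planned analysis is invalidated, and the open prescriber is inherent in a test-guided strategy. What changes is the strength of the claim about protection from bias. The conclusion rests on reading double-blind in its ordinary unqualified sense and on the blinding section being accurate about what prescribers are told.

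**What to change.** 1. In the abstract and in Trial design, replace the double-blind label with a statement by role: practitioners not blinded to POCT versus no POCT, but blinded to Arm 2 versus Arm 3; participants as was actually done; follow-up research assistants and statistician blinded.
2. In Randomization and blinding, reconcile the sentence on participants with the restrictive sentence on follow-up research assistants and the statistician. Correct the parenthesis so that the split concealed from practitioners is Arm 2 versus Arm 3.
3. List prescriber unblinding as a limitation for endpoints (a) and (b), in the article and in the results report.
4. As a precaution only, confirm that any slides still to be scored are read under the participant code without the arm. The participant timeline allows scoring within 6 months, and inclusion ended on 25 September 2025, so the last readings could fall as late as about 25 March 2026.

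Items 1 to 3 are wording and can be made after recruitment has closed. Item 4 is a confirmation. The real cost is a less favourable design label.

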**Fig. 1 Fig1:**
[figure not shown]
Consort diagram: Flow of participants from recruitment to follow-up

### Study setting

The study is conducted at Dhulikhel Hospital (DH) and seven of its outreach centers (ORCs) in Bagmati province, Nepal. DH is a non-profit, independent, non-governmental, tertiary hospital located in a semi-urban area of Nepal. It provides healthcare services to approximately 2.7 million people from diverse ethnic backgrounds across the country through 18 ORCs at the grassroots level [35]. The seven ORCs involved in the study were selected based on facility observation checklists (distance from DH, staffing, patient volume, infrastructure) with the aim of being representative of rural Nepal.

At DH, women presenting with concerns about VD are seen by obstetrics and gynecology consultants and resident doctors at the OPD. At the ORCs, these patients are attended by medical officers or obstetrics and gynecology residents.

### Participants

#### Eligibility criteria

Women 18 years and above who present with a main concern about VD at gynecology OPDs at DH or one of the selected ORCs. Exclusion criteria include current vaginal bleeding, known or suspected gynecological malignancy, prior participation in the same study, refusal to give informed consent, and unavailability of mobile phone contact for follow-up.

#### Recruitment and consent processes

The research assistant (RA) informs all women attending the gynecology OPD before 13:00 briefly about the study and checks for eligibility. Women expressing interest receive a detailed explanation, and written informed consent is obtained via signature or fingerprint with a witness for participants with limited literacy. The use of participant data and biological specimens is explicitly described.

### Interventions

#### Overview and rationale

The intervention targets the most clinically significant pathogens associated with abnormal VD: *Ct, Ng, Tv*, and BV. Untreated *Ct* and *Ng* can lead to serious health consequences, while overtreatment is associated with growing AMR. Although *Tv* and BV typically cause less severe complications, they impose a high symptom burden and are common among women presenting with bothersome VD. Both are treated with the same narrow-spectrum antibiotic, which is less likely to cause AMR [14, 36].

The intervention combines a highly accurate molecular test for *Ct* and *Ng* and a simpler POCT for *Tv* and BV, aiming to optimize diagnostic performance and resource use in Nepalese healthcare settings.

#### Trial arms

The trial consists of three parallel arms:Arm 1: Standard care (syndromic management). Health practitioners prescribe treatment based on clinical symptoms and signs, following Nepal’s national guidelines [15]. POCT results are not made available.Arm 2: POCT-guided treatment. Health practitioners receive POCT results for *Ct, Ng, Tv*, and BV and use this information to guide decisions in prescribing antibiotics.Participants under Arm 2 and Arm 1 view a general health education video on hand hygiene and dengue fever, produced by Save the Children, the Ministry of Health and Population, and Nepal Television.Arm 3: POCT-guided treatment plus psychosocial intervention. In addition to the POCT-guided treatment (as in Arm 2), participants in Arm 3 receive: an educational intervention consisting of a short video and leaflet with basic information on VD and appropriate antibiotic use. This intervention was developed using qualitative input from user groups, expert consultations, and with a local artist (article forthcoming). The participants are also screened for symptoms of anxiety and depression using content- and language-validated questionnaires. Those who screen positive are offered psychological counseling. In addition, all participants in this arm are asked whether they would like to be referred to a crisis management center for support related to DV [37–39].

